### Facultative biopsies

In the context of translational research, pre-treatment and/or post-treatment facultative biopsies will be obtained. For these biopsies, a separate informed consent is required. The main inclusion criteria for both facultative biopsies is the presence of a safely accessible disease localization of SDC, preferably metastatic disease.

### Dose modifications

In general, dose modifications are recommended for events that, if persistent, could become serious or intolerable, according to the Dutch Medicines Evaluation Board (CBG MEB). No dosage adjustments are required for participants with renal impairment using goserelin, bicalutamide, or dutasteride. Additionally, dutasteride should be used with caution in patients with mild to moderate hepatic impairment due to limited available information and is contraindicated in patients with severe hepatic impairment.

### Trial assessments

Patients will undergo treatment and response evaluations until progressive disease (PD), intolerable toxicity, or investigator and/or patient decision to withdraw. They will attend follow-up visits every three months in accordance with the standard of care for R/M SDC in the Radboudumc, which includes physical examination, blood analysis, and imaging via neck-, chest- and abdominal computed tomography (CT)-scans. Additional blood samples will be collected for translational research purposes. Additionally, eligible patients will be requested to complete multiple QoL questionnaires online using the electronic data management platform *Castor EDC (*http://www.castoredc.com*).* This includes three EORTC QoL questionnaires: the EORTC QLQ-C30 to assess the QoL of the cancer patients, the EORTC QLQ-H&N43 module designed for evaluation of head and neck cancer patients specifically, and the EORTC QLQ-SHQ22 to examine sexual health in patients undergoing anti-hormonal therapy [21–23]. The Visual Analogue Scale (VAS) will be incorporated to assess the presence of pain [24, 25]. Details regarding the complete assessment overview and laboratory parameters are provided in Tables 1 and 2, respectively.

**Table 1 Tab1:** Schematic overview of trial assessments at specific time points during the DUCT study

	**Time point in clinical trial**				
**Assessment**	**Screening / Baseline**	**Week 12**	**Week 24**	**Every 12 weeks until PD**	**PD**
Informed consent	X				
Eligibility assessment	X				
Physical examination + vital signs	X	X	X	X	
Electrocardiogram	X	X			
Neck-, chest- and abdominal CT-scan	X	X	X	X	
Clinical laboratory tests					
* Haematology parameters*	X	X	X	X	X
* Biochemistry parameters*	X^a^	X	X	X	X
* Thyroid function*	X				
* ctDNA*	X	X	X		X
Quality of life questionnaires					
* EORTC QLQ-C30* * EORTC QLQ-H&N43* * EORTC QLQ-SHQ22* * VAS*	X	X	X	X	X
Toxicity scoring (NCI CTCAE v.5.0)	X	X	X	X	
Facultative tumour biopsy					
* Coagulation parameters*	X^b^				X^b^

Abbreviations: *CT* Computed-tomography, *ctDNA* circulating tumour DNA, *PD* Progressive disease

^a^Including pregnancy test in pre-menopausal female participants

^b^This procedure contains a separate informed consent. Coagulation parameters are only measured in case of pre- and post-treatment facultative tumour biopsies

**Table 2 Tab2:** Schematic overview of laboratory parameters at specific time points during the DUCT study

		**Time point in clinical trial**				
**Category**	**Parameter**	**Screening / Baseline**	**Week 12**	**Week 24**	**Every 12 weeks from week 24**	**PD**
Haematology	Hemocytometry Automated differential	X	X	X	X	X
Biochemistry	Albumin Alkaline phosphatase ALT AST Bilirubin (direct) Bilirubin (total) Calcium Chloride CRP Gamma-glutamyl transferase LDH Magnesium Phosphate Potassium Sodium Urea	X	X	X	X	X
Kidney function	CKD-EPI-eGFR Creatinine	X	X	X	X	X
Hormones	Testosterone	X	X	X	X	X
Thyroid	Free thyroxine TSH	X				
Pregnancy	HCG blood	X^a^				
Coagulation	APTT INR	X^b^				X^b^
Research	ctDNA	X	X	X		X

Abbreviations: *ALT* Alanine aminotransferase, *AST* Aspartate aminotransferase, *LDH* Lactate dehydrogenase, *CRP* C-reactive protein,* CKD-EPI* Chronic kidney disease epidemiology collaboration, *PD* Progressive disease, *TSH* Thyroid stimulating hormone, HCG Human chorionic gonadotropin, *APTT* Activated partial thromboplastin time, *INR* International normalized ratio, *ctDNA* circulating tumour DNA

^a^In case of premenopausal female patients

^b^In case of pre-treatment and/or post-treatment biopsy

### Follow-up and discontinuation

Follow-up will continue for two years after the last inclusion, or until patient has been deceased, whichever occurs first. Patients can withdraw from the trial at any time without consequences. Once a participant withdraws, no further data or samples will be collected. However, participants who received at least one dose of study treatment, will undergo study-related medical record screening during follow-up independent of withdrawal. If a participant withdraws before start of study medication, there will be no study-related follow-up.

### Translational research

Goal of the translational part of this trial is to identify biomarkers with predictive potential, *i.e.*, markers that can predict response to CAB +/- dutasteride. Expression of relevant/potential biomarkers for resistance mechanisms of CAB will be determined at the transcriptome level. To perform the translational research part of this trial, different patient samples will be used, including blood (serum) and (fresh) tumour tissue. These patients’ samples will be stored in the salivary gland cancer biobank ‘Speekselklierkanker,’ which was previously approved by Committee on Research Involving Human Subjects (CMO) Radboudumc and up and running since 2017 (dossier number: 2017–3697). All samples will be managed in accordance with the biobank standard operating procedures of the Radboudumc.

From the (fresh) pre- and/or post-treatment tumour samples, total RNA will be extracted. These RNA samples will be used to measure the expression of genes involved in or regulated by AR signalling, or genes which affect AR signalling or resistance to CAB. The selection of genes will be based on prostate cancer research, and will, amongst others, include *AKR1C3, AR*, *AR-V7, CYP17A1, KLK3, SRD5A1, SRD5A2,* and *NAALADL2-AS2*. The gene expression profiles will initially be obtained using reverse transcription-quantitative polymerase chain reaction (RT-qPCR) technology, and a full RNA sequencing-based transcriptome analysis will be considered if results are negative.

Serum testosterone levels will be measured at baseline, during therapy, and after therapy to determine its predictive value for treatment response. In addition, blood samples will also be examined for longitudinal circulating tumour DNA (ctDNA) levels to evaluate whether treatment response and/or failure can be predicted. CtDNA levels will be assessed using an in-house developed and validated hybrid-capture based next-generation sequencing test, as described recently [26, 27].

## Sample size

### Cohort A – CAB-naïve patients

Sample size is calculated based on first primary endpoint, the ORR. Prior data indicate that the response rate among controls (CAB therapy) is 0.417 [4]. If the response rate for experimental subjects is 0.700, we will need to study 37 patients in each arm to be able to reject the null hypothesis that the response rates for experimental and control subjects are equal with probability (power) 0.8. The type I error probability associated with testing our hypothesis is allowed to be 0.1. We will use an uncorrected chi-squared statistic test to evaluate this null hypothesis. Sample size calculation was performed with PS: Power and Sample Size Calculations, version 3.

### Cohort B – CAB-resistant patients

The Simon’s two-stage design, optimal version, will be applied for enrolment in cohort B [28]. The null hypothesis that the true ORR is 5% will be tested against a one-sided alternative, as prior data indicate that the response rate on second-line chemotherapy in patients with SGC is 5% [29]. The combination of the triple therapy will be considered effective and worth of further evaluation if the ORR is at least 20%. In the first phase, nine participants will be accrued and if in at least one of these nine participants a partial or complete response will be observed, fifteen additional participants will be accrued in the second phase of enrolment to a final overall sample size of 24 participants. In case no responses are observed in the first nine patients, cohort B will be closed early for futility. If at least three out of 24 participants confirmed responses are observed, the null hypothesis will be rejected in favour of this triple therapy and this therapy will be considered promising and worthy of further investigation. This design yields a type I error rate of 0.10 and power of 0.8 when the true response rate is 0.20.

### Oversight and monitoring

A Data Safety Monitoring Board (DSMB) is installed to (i) monitor indications of treatment-related harm in both cohort A and B; (ii) review any (serious) adverse events occurring in men and women in both cohort A and B; and (iii) decide continuation of patients recruitment, including the possibility of terminating recruitment for the entire trial or specific cohorts (B) and/or participant subgroups (women). The DSMB is represented by three independent and (inter-)national expert members: an otorhinolaryngologist/head and neck surgeon, a medical oncologist, and a biostatistician. A trial update, including safety measurements, is provided every three months in accordance with the DSMB charter. Furthermore, after completion of the initial phase of cohort B an interim analysis will be provided to the DSMB, according to the results and their recommendations accrual in cohort B will be continued or discontinued. Besides the established DSMB, a clinical research monitor mandated by the Sponsor will monitor the trial according to the Guideline Quality assurance of research involving human subjects for studies with a negligible risk.

### Randomization and data collection

Randomization only occurs for cohort A and will result in the allocation of the control arm and experimental arm in a 1:1 ratio using *Castor EDC*. Randomization to both arms will be performed by variable block randomization (block sizes 2, 4, and 6) and participants will be stratified by sex (male *vs.* female). All data is collected by data managers using the electronic case report form (eCRF) *Castor EDC* to document eligibility, safety and efficacy parameters, compliance to treatment schedules and parameters necessary to evaluate trial endpoints. Patient data will be pseudonymized by allocating a unique patient record ID to all patients. Data will be collected and processed in accordance with the General Data Protection Regulation (EU) 2016/679 and in compliance with national requirements on data protection (*i.e.*, Dutch Personal Data Protection Act). Translational research samples will be stored in the Radboudumc for 25 years in accordance with Dutch national law.

### Statistical methods and data analysis

The primary objective is the best ORR. All evaluable subjects will be included in the analyses. ORRs will be reported as fractions with their corresponding two-sided 95% confidence intervals (CI) per arm. In cohort A, the null hypothesis of equal ORRs in the two arms will be evaluated with a chi-squared test at a significance level 0.10. The difference of the ORRs in the two arms will be reported with a corresponding 90% CI. The (second) primary outcome, the DoR will be reported using descriptive statistics, including median ± CI to draw exploratory clinically relevant conclusions. The data of cohort B will be reported using descriptive statistics (means or medians including CI as applicable).

Patient characteristics will be summarized using means (with standard deviations) or medians (with inter quartile range). Both PFS and OS will be estimated by Kaplan–Meier curves, and for cohort A the difference in survival between arms being evaluated with the log-rank test. CBR and safety will be reported using descriptive statistics (means or medians as applicable) both for cohort A and B. The safety profile will be based on the incidence of SAE’s according to NCI-CTCAE v.5.0. Possible associations between expression of molecular targets and efficacy will be analysed using descriptive statistics, and uni- and multivariable analyses for both cohorts. All patients with a valid baseline and at least one follow-up QoL questionnaire will be included in the analysis per cohort. The baseline questionnaire is considered valid if filled out and dated by the patient before the starting date of trial treatment. Reasons for missing baseline and follow-up questionnaires will be assessed. To evaluate the differences between the treatment groups, with respect to the effect of treatment burden on life-quality during the treatment, the repeated measures of the QLQ-C30 and QLQ-H&N43 will be analysed using mixed effect models. Molecular data will be analysed and reported in accordance with in-house protocols.

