## Objectives

The primary objectives of the DUCT study are to evaluate the ORR of dutasteride in combination with CAB patients with R/M SDC together with the duration of response (DoR), and to evaluate whether addition of dutasteride counteracts therapy resistance in patients who previously have been treated with anti-hormonal therapy. The ORR is defined as the proportion of participants who have CR or PR determined per RECIST v1.1. The DoR is defined as the time from first tumour assessment at which the objective response was recorded as CR or PR that is subsequently confirmed until PD determined per RECIST v1.1, or death from any cause, whichever occurs first.

The secondary objectives are:To assess the PFS, defined as the time from trial enrolment until date of first documented disease progression per RECIST v.1.1, or death due to any cause, whichever occurs first.To assess the OS, defined as the time from trial enrolment to the date of death due to any cause.To assess the clinical benefit rate (CBR), including confirmed CR or PR at any time or stable disease (SD) of at least 6 months determined per RECIST v.1.1.To assess the quality of life (QoL) of patients treated with anti-hormonal therapy, according to approved EORTC (QLQ-C30, QLQ-H&N43, QLQ-SHQ22) and VAS questionnaires.To assess the safety profile of dutasteride combined to CAB therapy by the incidence of severe adverse events (SAE) according to National Cancer institute Common Terminology Criteria for Adverse Events (NCI-CTCAE) version 5.0.To explore expression of molecular markers (*e.g., AR*, *SRD5A1* and *SRD5A2*) in patients’ blood and tumour samples to monitor treatment efficacy.

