### Expected limitations

It is important to acknowledge the anticipated limitations inherent to this study. Firstly, our study is a single-institution trial, which may pose challenges in terms of patient recruitment, especially for a rare cancer such as SDC. However, our institution serves as a tertiary referral centre for SGC in the Netherlands. This specialized focus on SGC care not only enhances patient enrolment opportunities but also facilitates research endeavours concerning this uncommon malignancy. Unfortunately, inclusion in cohort A has been closed based on limited accrual (*n* = 2) since April 18, 2024. Secondly, designing and setting up clinical trials for rare diseases presents a unique challenge as it necessitates an acceptable balance between attaining a robust level of scientific evidence and ensuring the practicality of the trial in terms of trial size and duration [30]. Therefore, the Type I error probability for testing our hypothesis is adjusted to 0.1 instead of the conventional 0.05. Lastly, the data related to dutasteride in combination with CAB in castration resistant PCa is limited. Nevertheless, our translational research on SDC provides a compelling rationale suggesting the potential added value of inhibiting SRD5A1 as an adjunct therapy.

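### The only quality-of-life model is a between-group comparison that cohort A can no longer support, while cohort B, the only cohort with usable data, is assigned descriptive summaries that can drift favourably as patients progress

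*Protocol article*

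**What the plan says.** All references are to the Protocol article.

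- **Objective.** A secondary objective under Objectives is "To assess the quality of life (QoL) of patients treated with anti-hormonal therapy". It is not framed as a comparison.
- **Model.** Under Statistical methods and data analysis, "the repeated measures of the QLQ-C30 and QLQ-H&N43 will be analysed using mixed effect models", and the purpose given is "To evaluate the differences between the treatment groups, with respect to the effect of treatment burden on life-quality during the treatment". No other QoL model is named.
- **Cohort B.** The same section states: "The data of cohort B will be reported using descriptive statistics (means or medians including CI as applicable".
- **Analysis set and missing forms.** "All patients with a valid baseline and at least one follow-up QoL questionnaire will be included in the analysis per cohort", and "Reasons for missing baseline and follow-up questionnaires will be assessed". No handling of forms missing after progression is stated.
- **Groups.** Randomization and data collection confines randomisation to cohort A. Expected limitations reports that "inclusion in cohort A has been closed based on limited accrual", with n = 2, as of April 18, 2024. Cohort B receives a single regimen and has at most 24 patients.
- **Schedule.** Table 1 marks all four QoL instruments at baseline, week 12 and week 24, then "Every 12 weeks until PD", and also in a separate PD column. Nothing is scheduled after PD.

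**The concern.** The objective is to describe QoL under treatment. The one method that uses each patient's repeated forms is reserved for a contrast between groups, and with two patients in cohort A that contrast can no longer be estimated. Reading the treatment groups as cohort A against cohort B does not help, because one side would still have two patients. What remains for the cohort with data is a set of means or medians.

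Because forms stop at PD, the patients behind each later summary are a subset. If poorer QoL goes with earlier progression, that subset had better QoL from the start. Its mean then moves in the favourable direction although no patient has improved, and a reader could take this as QoL being maintained or improved on triple therapy.

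**Working it through.** **Plan's own figures.** The article states no QoL figure to reproduce. The design figures that fix the group sizes do reproduce. For cohort A, 37 per arm at 0.417 against 0.700 with two-sided alpha 0.10 and no continuity correction gives power 0.80. For cohort B, at least 1 response in 9 and then at least 3 in 24 gives an exact type I error of 0.093 at 5% and power of 0.805 at 20%. The chance of stopping at nine patients is 0.95^9 = 0.63 at a true response rate of 5% and 0.80^9 = 0.13 at 20%.

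**Assumed inputs** (none is in the documents unless noted):

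- n = 24; a 0-100 scale on which higher is better; between-patient SD 15, residual SD 12; no true change in any patient.
- Progression hazard for a patient whose QoL lies z SDs above average: λ(z) = (ln 2 / m)·e^(−βz), where m is the median PFS at z = 0.
- m = 3, 5 or 8.8 months. The last is the Background's figure for CAB in advanced SDC; the other two allow for shorter control in resistant disease.
- β = 0.5 gives a hazard 1 − e^(−0.5) = 39% lower per SD of better QoL; β = 0.25 gives 22%.
- Progression is found at the next 12-weekly visit, and the PD form is counted at that visit.

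**Formula.** With the PD form counted, the patients contributing at week w are those who were progression-free at week w − 12. Put t = w − 12 weeks in months (12 weeks = 2.76, 24 weeks = 5.52) and S(z) = exp(−λ(z)·t). Then, averaging over a standard normal z:

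- expected drift of the visit mean from baseline = 15 × E[z·S(z)] / E[S(z)]
- expected number contributing = 24 × E[S(z)]

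**Results by numerical integration** (drift in points, expected number in brackets):

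| Case | Median PFS | Link | Week 12 | Week 24 | Week 36 |
|---|---|---|---|---|---|
| a | 5 months | 39% | 0 (24) | +2.9 (15.9) | +5.3 (11.0) |
| b | 3 months | 39% | 0 (24) | +4.6 (12.4) | +8.1 (7.0) |
| c | 5 months | 22% | 0 (24) | +1.4 (16.3) | +2.8 (11.1) |
| d | 8.8 months | 39% | 0 (24) | +1.7 (18.9) | +3.3 (15.1) |
| no link | 5 months | 0% | 0 (24) | 0 (16.4) | 0 (11.2) |

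Simulation of the same cases agrees to within about 0.1 to 0.2 points at week 24. Rounded, the drift is about 1.5 to 4.5 points at week 24 and 2.8 to 8 at week 36. Week 12 shows none because every patient has either a week-12 form or a PD form by then. On a symptom scale the signs reverse.

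**Within-patient change.** If nobody changes, each patient's change from baseline is a difference of two residual errors. It does not depend on z, so its mean is zero at every visit whoever remains.

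**Mixed model on the same forms.** y = visit effect + patient effect + error. With these SDs the intraclass correlation is 225 / (225 + 144) = 0.61, so earlier forms carry much of the information on who has left. Simulated trials of 24 patients gave a week-24 estimate of about +0.3 to +1.0 across the four cases, against a true value of 0. In case (a) its sampling SD was 4.1 to 4.3, against 4.5 to 4.6 for the raw visit mean.

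**If patients truly decline.** This check assumed a true loss of 8 points by week 48, a median PFS of 24 weeks and a hazard that doubles per SD of worse latent QoL (one run of 1,500 patients, PD form included). The raw visit mean read +7.1. A model with random intercept and slope read −4.8. The model is closer to −8 but does not reach it.

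**The case against.** The case against a stronger claim is good, and much of it stands.

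- **Progression-free patients only?** A reader might infer that later summaries cover only patients who have not progressed. Table 1 also schedules every instrument at PD. Leaving that form out would put the week-24 drift at the table's week-36 values (+2.8 to about +8); counting it roughly halves that.
- **Raw visit levels?** The article does not say whether the means or medians are visit levels or changes from baseline. Requiring a baseline form fits either. Change from baseline is free of this bias when nobody changes, though not when decliners progress sooner.
- **Always upward?** No. The drift needs a link between QoL and progression, which the documents do not give. It runs downward on symptom scales, and observed means can still fall when the true decline is steep.
- **Small against noise.** At week 24 the drift in cases (a), (c) and (d) is below the visit mean's sampling SD, which is about 4 to 4.6. That is true, but a bias of this kind does not show in the confidence interval.
- **Condensed article.** Descriptive reporting of a secondary endpoint in at most 24 patients is legitimate, and the full protocol or SAP may add detail. Protocol version 4.0 (February 21, 2024) also predates the closure of cohort A. The point survives because the article is not silent: it assigns the model to a contrast that cannot be made and a descriptive method to the cohort with data.

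**Conclusion.** The point holds as a modest, inexpensive improvement to a secondary endpoint, not as an error that invalidates the plan. The text supports two statements: the only QoL model has no usable comparison once cohort A has closed with two patients, and cohort B's stated method is descriptive, with collection ending at the PD form. The size is conditional. If the summaries are visit levels and worse QoL goes with earlier progression, they drift favourably by about 1.5 to 4.5 points at week 24 and 2.8 to 8 at week 36 under the assumed inputs, and not at all at week 12. Without that link, or with within-patient change when nobody changes, there is no bias. The documents do not support saying that the arms never existed, that only progression-free patients are summarised, or that QoL will necessarily appear to rise.

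**What to change.** In Statistical methods and data analysis, extend the planned mixed effect model to cohort B:

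- fixed effect of visit and random patient effect, fitted to all available forms, with the PD form entered at the week it was completed;
- modelled mean change from baseline with its CI as the QoL result;
- raw visit summaries only as a supplement, each with the number of patients contributing;
- the two cohort A patients listed individually, without a between-arm comparison.

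Add a sentence saying that no forms are collected after PD and how this limits interpretation.

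**Cost.** Wording only: no new data, visits or patient burden. The model assumes that missingness is explained by the observed forms, so it reduces the bias rather than removing it. It must also stay simple, with at most 24 patients, or nine if cohort B stops after its first stage.
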